**Fig. 1 Fig1:**
[figure not shown]
Postulated Causal Pathways CBT-Specific Factors include exposure and development of coping skills. Common factors include the strength of the therapeutic alliance, clinician relatedness, and rewards associated with treatment. Medication-Specific Factors include direct effects of fluoxetine on brain circuits. Functional Outcomes include improved social relationships, better family and academic functioning, and improved self-esteem, which also function as natural reinforcers, or rewards. Vertical arrows from the Contextualizing Factors represent moderation of the association (shown as an oblique arrow) of a treatment modality with the indicated set of mediators. These contextual factors include Illness Factors such as comorbid illnesses, baseline anxiety severity, and family history of anxiety, as well as Cultural Factors, which include ethnicity and SES

**Table 1 Tab1:** Core Functions and Forms [76] for *Coping Cat*

CORE FUNCTION	CORRESPONDING FORMS

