
#### Contextualizing factors

Also termed patient “tailoring variables”, these factors modify treatment response. Candidates for tailoring variables include baseline individual, family, and context characteristics, some of which relate directly to child anxiety and its clinical portrait: ethnicity [30], SES [32], past treatment response [29, 31], and family history of anxiety; and variables that are potentially modifiable, such as overall symptom severity [29, 31], functional impairment [29, 31], the nature and severity of comorbid illnesses, treatment fidelity and adherence, and treatment setting (community or university; primary pediatric or specialty mental health clinic).

We theorize that demographic characteristics such as ethnicity [30] and SES [32] will function as *cultural factors* that will influence the nonspecific factors of therapeutic alliance, clinician relatedness, and treatment adherence. Data from the CAMS trial support these hypotheses. In CAMS, African-American youths attended fewer CBT and medication management sessions, and they were rated by therapists as less involved and compliant with treatment and, possibly as a consequence, as showing a lower level of mastery of CBT concepts [41]. Controlling for these process factors and SES eliminated racial differences in outcome. Similarly, patient nonadherence (poor attendance, low homework completion, poor compliance in session) was associated with number of parents present in the home (with the best outcomes for two-parent families), although indices of nonadherence varied in their power to predict clinical outcomes [124]. In contrast, we expect the modifying effects of *illness-related factors*, such as depression and other comorbid illnesses, baseline anxiety severity, and family history of anxiety, will operate through their impact on the *Coping Cat*-specific factors, exposure and development of coping skills [29, 31, 119]. Table 2 specifies how we will measure each of these contextualizing constructs.

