### Study design

This will be a single-blind [126, 127] SMART design [51, 52] of 24-week treatment duration that will employ two sequential levels of randomization, one in each of two 12-week stages of the study **(**Fig. 2**)**.

#### Stage 1

404 children ages 8–17 who have an anxiety disorder will be randomized 1:1 to receive 12 weeks of either the medication fluoxetine in upward-titrated dosages or weekly CBT implemented using the *Coping Cat* CBT model [128].

#### Stage 2

All participants who do not remit in Stage 1 will be randomized 1:1 to either (1) optimization of their Stage 1 treatment, or (2) optimization of their Stage 1 treatment and addition of the other treatment modality (Fig. 2). Study assessments will be obtained at baseline, week 12, and week 24. A small subset of measures (SCARED-41, and the Pediatric Side Effect Questionnaire) will also be obtained at weeks 6 and 18. Participants who remit during the first 12 weeks of treatment will continue maintenance-level therapy with the single-modality treatment received in Stage 1. If a participant who achieved clinical remission during the first 12 weeks of treatment relapses at the week 18 study assessment (defined as having a SCARED total score of ≥25), the participant will be referred to the treating clinician to restart or slightly intensify the previous treatment assigned in Stage 1 of the study. Following conclusion of the 24-week trial, we will follow and obtain all the same study assessments in all participants quarterly for at least 12 months [44, 126, 127].

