(3) Group main effect ESs were then computed for a Stage 1 remission rate of 40%. Our estimated Stage 1 remission rate of 40% is a conservative estimate based on the CAMS remission rate of 35% achieved for ethnic minorities, when applying remission criteria less stringent than ours [30]. In CAMS, the 12-week remission rate was also approximately 10% higher in medication-only compared to CBT-only. We used this 10% difference in these calculations to compute ESs and resulting sample size estimates. For Main Effect 1 (start with medication vs start with CBT), ESs for all 3 medication or CBT groups (1: remitter; 2: non-remitter➔optimize monotherapy; 3: non-remitter➔medication+CBT) were computed as a weighted average of the group-specific ESs. Weights were the remission rate, with the non-remitter weight (1 minus remission-rate) split equally among the 2 randomized non-remitter groups (reflecting 1:1 Stage 2 randomization among non-remitters). For Main Effect 2 (among Stage 1 non-remitters, optimize Stage 1 treatment vs add the other treatment), ESs were computed as a weighted average of the ESs for monotherapy optimizers (medication+, CBT+) and a weighted average of the combined (medication+CBT, CBT + medication) groups. These weights were again 0.5*(1- remission-rate).

[4] We then computed the sample size required to detect Main Effect 2 (optimize monotherapy vs add the other therapy in non-remitters) at 80% power and tested at a 2-sided alpha = 0.05. From our computations above, the Main Effect 2 ES was approximately 0.40 SD, requiring a sample size of 194 participants among Stage 1 non-remitters. Increasing the sample size of 194 by the non-remission rate (N divided by non-remission rate) and by the estimated 20% dropout rate, yielded a sample size of 404 (202 per group) for Stage 1 remission rates of 40%. Randomizing 404 participants, with an estimated 324 finishing the trial and a remission rate of 40%, will provide the ability to detect an overall Main Effect 1 (medication first versus CBT first) ES of ≥0.31 SD with 80% power.

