#### HTE analysis plan

Dividing the total sample into pre-defined subgroups, we will use analytic methods detailed above to estimate treatment effects across subgroups. Forest plots of mean treatment group differences with confidence intervals for each subgroup will be completed to graphically evaluate uniformity of treatment effect. In the total sample, we will first add the subgroup as a main effect covariate. Evaluation of the subgroup main effect will test over the entire sample (combined intervention groups) whether and to what extent outcomes in general differs by SES, ethnicity, comorbid depression, social anxiety disorder, and treatment setting.

We will employ Q-learning as our primary approach to testing the heterogeneity of treatment effects. This is a regression approach recommended for SMART data to identify tailoring variables that modify treatment responses and suggest enhancements to the sequential decision-making of an adaptive intervention [197]. In this 2-stage SMART design with a continuous trial outcome, Q-learning with linear regression will be used in 2 steps. In step 1, the Stage 2 decision rule will be optimized among Stage 1 non-remitters, identifying individual variables that significantly modify the Stage 2 randomization effect. In step 2, the Stage 1 decision rule will be optimized, controlling for the optimized Stage 2 intervention and identifying individual variables that significantly modify the Stage 1 randomization effect. This approach therefore may suggest a more tailored adaptive intervention that could be evaluated in a future SMART study.

As there will remain clinical subgroups of primary interest to clinicians, we will also assess in a secondary analysis the randomized treatment-by-subgroup (e.g., treatment-by-SES group) interaction terms to estimate and test for differences in treatment effects (Main Effects 1 & 2) by subgroup. Estimating treatment effects across our carefully pre-defined subgroups, we will use forest plots of mean treatment group differences with confidence intervals for each subgroup to show subgroup-specific effects and graphically evaluate uniformity of treatment effects.

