With an estimated 20% dropout, we will be able to detect the following effect sizes for Main Effect 1 (total *n* = 324) in various subgroups by sample representation (n): (1) Effect Size = 0.40 for 60% representation (*n* = 194); (2) Effect Size = 0.44 for 50% representation (*n* = 162); (3) Effect Size = 0.50 for 40% representation (*n* = 130). For Main Effect 2 (total n = 194), we will be able to detect: (1) Effect Size = 0.52 for 60% representation (*n* = 116); (2) Effect Size = 0.58 for 50% representation (*n* = 96); (3) Effect Size = 0.64 for 40% representation (*n* = 78). Subgroup interactions will be tested formally; with the total anticipated sample size of 324 to complete the 24-week intervention, we will have 80% power to detect subgroup differences in treatment effect sizes of ~ 0.65 and higher for Main Effect 1, and ~ 0.8 and higher for Main Effect 2.

In additional exploratory analyses, we will use latent class/profile analysis to model heterogeneity of outcome response patterns, assuming categorical latent variables (latent groups) for response. Latent class/profile analysis has been proposed as an alternative to subgroup analysis in clinical trials. As an exploratory analysis, it uses observed data (e.g., clinical characteristics, randomized treatments) to identify latent group classifications that may suggest individual characteristics related to greater responses to treatment [205].

In addition to assessing the effects of telehealth delivery of treatment on outcomes, we will assess whether the percentage of treatment sessions conducted via telehealth moderates treatment outcomes. This test will tell us whether discontinuities in telemedicine use over the course of the study or within individual patients has influenced our findings. We will also assess whether session attendance and trial completion differ by degree of participation in telehealth vs in-person intervention.

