**Fig. 6 Fig6:**
[figure not shown]
Tests of Mediation. X = Treatment. M = Proposed Mediator. Y = 24-week outcomes. a = coefficient for correlation of X with M (M = aX). b = coefficient for correlation of M with Y (Y = bM). Y = c X = c’ + ab (the total effect of X on Y). M = a X (the effect of X on M). Y = c’ X + b M (direct effect of X on Y). a x b (mediation effect). Algebraic sign of a x b x c (type of mediation – complementary or suppressive)

We then will assess whether mediation is partial or complete, and whether it is complementary (i.e., the direct and mediated effects are in the same direction on the outcome Y and therefore have the same algebraic sign) or suppressive (the direct and mediated effects are in opposing directions on outcome Y and therefore have opposite signs). We will assess the significance of the direct effect (coefficient c_2_ in eq. 3): statistical significance of this term will signify that mediation by M is partial [206, 207]. We will also assess the algebraic sign of the product a*b*c to determine whether mediation is complementary or suppressive [206, 207].

Finally, a complex mediation model that jointly estimates multiple mediating outcomes and incorporates the correlations among mediators and joint effects of mediators on trial outcomes will ultimately be used to test and understand the mechanisms of the CBT and medication interventions on anxiety outcomes. Moderator effects of the Contextualizing Factors will be tested as described under “Heterogeneity of Treatment Effects”.

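### The pathway model has context moderating the effect of treatment on the mediators, but every moderation test specified uses the trial outcome, so these exploratory hypotheses have no matching test

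*Protocol article*

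**What the plan says.** All references are to the Protocol article.

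- **Causal model.** The Fig. 1 legend says the arrows from the contextual factors "represent moderation of the association (shown as an oblique arrow) of a treatment modality with the indicated set of mediators". This places moderation on the treatment-to-mediator path.
- **Pathway hypotheses.** Under Contextualizing factors, ethnicity and SES are cultural factors "that will influence the nonspecific factors of therapeutic alliance, clinician relatedness, and treatment adherence". By contrast, comorbidity, baseline severity and family history are expected to work through the Coping Cat-specific factors, exposure and coping skills.
- **Mediation equations.** Mediation analyses writes out three regressions. The second, for the mediator, is M = aX + e2. Age and sex are the only covariates in any of the three.
- **Where moderation goes.** The same section ends: "Moderator effects of the Contextualizing Factors will be tested as described under" the heading on heterogeneity of treatment effects.
- **What that heading specifies.** The HTE analysis plan sets out subgroup main effects, Q-learning on a continuous trial outcome, and the statement "we will also assess in a secondary analysis the randomized treatment-by-subgroup (e.g., treatment-by-SES group) interaction terms", which concern Main Effects 1 and 2. The power it states is for outcome interactions only: about 0.65 SD for Main Effect 1 and about 0.8 SD for Main Effect 2.

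**The concern.** The hypotheses separate two routes: culture through the common factors, illness through the CBT-specific ones. Only a model with the mediator on the left-hand side can show whether context changes what treatment does to that mediator. An interaction on the outcome mixes moderation of the treatment-to-mediator path, the mediator-to-outcome path and the direct path, and it carries no label for the mediator involved.

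What is at stake is interpretation. Process evaluation promises to assess the causal pathways of Fig. 1. With the analyses as written, a positive outcome interaction could come from any path, and a null one would say little about the path that the model names.

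**Working it through.** **1. Side by side.**

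| Item | Hypothesis | Specified analysis |
|---|---|---|
| Dependent variable | Mediator (alliance, relatedness, adherence, CBT-specific factors) | Trial outcome |
| Term needed | Treatment × context in the mediator equation | Treatment × subgroup in the outcome equation |
| Mediator equation | Effect of X on M differs by W | M = aX + e2, no W and no XW |

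**2. What the outcome interaction estimates.** Let M = a1X + a2W + a3XW and Y = c2X + bM. Substituting, the XW coefficient for Y is a3 × b. If the direct path is also moderated by c3, it becomes c3 + a3 × b. The outcome test therefore cannot isolate a3. When only the treatment-to-mediator path is moderated and standardised |b| is below 1, it also sees a smaller effect.

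**3. The plan's own interaction figures.** Inputs:
- Stage 1 allocation: participants "will be randomized 1:1 to receive 12 weeks of either the medication fluoxetine" or CBT.
- Sample size: "with the total anticipated sample size of 324 to complete the 24-week intervention".
- Alpha and power, from Sample size and power: "at 80% power and tested at a 2-sided alpha = 0.05".

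With SD = 1 and subgroup share f, SE = √[4/(Nf) + 4/(N(1−f))], and the detectable difference is (1.96 + 0.84) × SE.

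- N = 324, f = 0.5: SE = 0.222, detectable 0.62. For f = 0.4 it is 0.64 and for f = 0.3 it is 0.68.
- N = 194, f = 0.5: SE = 0.287, detectable 0.80. For f = 0.4 it is 0.82.

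The stated values of about 0.65 and 0.8 reproduce.

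**4. Power for a moderated path.** The documents give neither a3 nor b, so both are assumptions, in SD units. Power = Φ(δ/SE − 1.96) + Φ(−δ/SE − 1.96), with δ = a3 for the mediator test and δ = a3 × b for the outcome test. N = 324, f = 0.5, SE = 0.222, unadjusted alpha 0.05:

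| a3 | Test on mediator | Outcome, b = 0.2 | b = 0.3 | b = 0.5 | b = 0.7 |
|---|---|---|---|---|---|
| 0.3 | 27% | 6% | 7% | 10% | 16% |
| 0.5 | 61% | 7% | 10% | 20% | 35% |
| 0.65 | 83% | 9% | 14% | 31% | 53% |
| 0.8 | 95% | 11% | 19% | 44% | 71% |

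For a3 = 0.5 and b = 0.3, the outcome interaction is 0.5 × 0.3 = 0.15 SD.

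**5. Uneven subgroups.** The sample is planned to be predominantly disadvantaged and of ethnic minority background, so equal halves on ethnicity or SES are doubtful. At 80/20, SE = 0.278. The mediator test at 0.5 SD then has Φ(0.5/0.278 − 1.96) = Φ(−0.16), or about 44%, down from 61%. False-discovery-rate control, required under Multiplicity for secondary, exploratory and subgroup analyses, lowers both sets of figures further.

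**6. Which mediators allow the test.** Table 2 schedules the Outcome and Session Rating Scales and the Child Avoidance Measure monthly, and self-efficacy at baseline, 12 and 24 weeks, with no restriction by arm. The therapist-rated exposure index comes only from CBT sessions (Factors specific to Coping Cat CBT; CBT fidelity measurement). It has no value in the fluoxetine arm during Stage 1, so neither its a-path nor the moderation of that path can be estimated between arms.

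**The case against.** The strongest reply is that aim and test agree. Specific aims sets out to explore moderation of Main Effects 1 and 2 and of their interaction, which is outcome-level, and the pre-specified HTE hypotheses also concern outcomes. On this view the path wording is background theory. That stands as a reason to keep the point modest. However, the article says it will assess the Fig. 1 pathways and writes out the mediation models for doing so, so the mismatch lies inside its own text.

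A second reply is that the cross-reference, sitting in the mediation section after a more complex multi-mediator model, could mean that the HTE methods apply to the mediators. The section also says it will follow the developing literature on mediation in SMART designs, and a separate analysis plan may give detail. This is possible, but the reader has to supply it: the HTE analysis plan names only Main Effects 1 and 2 and the continuous trial outcome. If that is the intention, a sentence would settle it.

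A third reply is that the remedy is incomplete, because the exposure index cannot be compared between Stage 1 arms and power is modest. Both parts are correct and should be stated in the plan.

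A reader might infer from the 10% cell that the pathway hypotheses are tested at about 10% power. The documents do not support that. The figure belongs to the outcome interaction, not to a test of the pathways, and it depends on assumed values of a3 and b that the article does not give. Nor does any passage say that a null outcome interaction will be reported as absence of moderation.

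**Conclusion.** The point holds as a mismatch between hypothesis and analysis. The model puts contextual moderation on the treatment-to-mediator path, the mediator equation has no term for it, and the section it is referred to tests only the outcome. The exploratory pathway hypotheses therefore have no matching test in this document.

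The structural conclusion needs no numerical assumption. The size does: path shifts of 0.3 to 0.8 SD, b of 0.2 to 0.7, n = 324, equal subgroups, unadjusted alpha and no moderation on other paths. Within those, power is about 6% to 71% on the outcome against 27% to 95% on the mediator.

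A reader might go further and infer that the stated detectable interactions are wrong or that the main results are weakened. Neither follows: the stated figures reproduce, and the primary and secondary outcome tests and the sample size are untouched.

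**What to change.** 1. For mediators measured in both arms, replace the second mediation equation by M = a1X + a2W + a3XW plus covariates. These are the alliance and relatedness ratings, the Child Avoidance Measure, self-efficacy and, as the adherence measure, session attendance if it is put on a common scale.
2. Fit it only for the hypothesised context-mediator pairs. Report a3 and the index of moderated mediation, a3 × b, with the bootstrap intervals already planned.
3. Place these tests in the false-discovery-rate family. If power is quoted, give a range with its assumptions.
4. Keep the outcome-level HTE tests as a separate question, and reword the cross-reference so that it no longer stands in for the pathway test.
5. State that moderation through the therapist-rated exposure index cannot be estimated between Stage 1 arms, because it is collected only in CBT sessions.

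The cost is a few more regressions on data already scheduled and some plan wording. The downside is a few more exploratory tests with modest power.

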### Data safety monitoring board (DSMB)

Our data safety-monitoring plan is designed to ensure the safety of participants, the validity of the data collected, and the appropriate termination of the study in the event that significant benefits or risks are uncovered, or if it appears that the trial cannot be concluded successfully. We will convene a Data Safety Monitoring Board (DSMB) that is fully independent from the sponsor and competing interests. The DSMB will have the authority to recommend termination of the trial to the principal investigator and funding agency if it judges that a specific action is not in the best interest of study participants or that the conduct of study processes are unlikely to lead to sound scientific results. The board will also review subject burden levels associated with data collection tasks. The board will meet every six months to review study progress and adverse events. The PI and study staff will provide to the DSMB all patient data collection materials as well as a semi-annual summary report on patient outcome tracking. They also will immediately report to the DSMB any adverse patient or caregiver outcomes. The DSMB will be authorized to request any additional information or study materials it deems appropriate. All participants will be provided contact information for the DSMB to register complaints or other problems.

The DSMB will comprise three health care researchers, who are voting members, and one non-voting caregiver. They are:
[name] MD, Chief, Section on Development and Affective Neuroscience in the National Institute of Mental Health Intramural Research Program. He is an expert in the neurobiology and treatment of pediatric anxiety and mood disorders. He is chair of the DSMB.[name] [name]., Associate Professor in the Department of Psychology at Arizona State University. He is an expert in real-world psychosocial interventions for pediatric anxiety disorders.[name]. Vice President and Biostatistician, The Emmes Company, LLC, Rockville, MD. He is an expert clinical trials statistician. He is the clinical trials statistician for the Pediatric Trials Network.[name]: non-voting community stakeholder

The charter for the DSMB is available from either the study PI or the DSMB chair upon request. No independent audits for the study are planned.

### Ethics

This study protocol was reviewed and approved under the SMART Institutional Review Board (IRB) mechanism, with Children’s Hospital Los Angeles the designated lead IRB. Parents will provide informed written consent for their child’s participation, and the child will provide informed written assent (see Supplementary Material for the consent and assent forms for the clinical trial and ancillary study), which will be obtained by trained study personnel. Post-trial care will be determined through routine clinical decision-making of the patient and treating clinician, and it will be paid through the patient’s usual insurance mechanisms. No compensation will be provided for those who suffer harm from trial participation. Any changes to the study protocol will need to be reviewed and approved by PCORI and the IRB. Changes will be documented within ClinicalTrials.gov and communicated to all relevant parties (e.g., investigators, DSMB, and trial participants).

